### 4.9. Adverse Events

This is a minimal-risk study that involves the use of a commercially available dietary supplement. Thus, we do not anticipate any adverse events related to the study protocol. Nonetheless, the subjects will be systematically monitored for adverse events in person and via telephone interviews. They will be instructed to contact investigators if any side effects occur. All adverse events will be reported to the medical director of the Medical University Hospital in Lodz (Poland) within 24 h.

### 4.10. Statistical Analyses

#### 4.10.1. Sample Size Calculation

Based on the effects observed in the previous study, in which we used a similar probiotic and prebiotic combination, but without microencapsulated sodium butyrate, in IBS patients [27], we have estimated that a sample size of 35 participants per group would be required to reach clinical significance. With an estimated drop-out ratio of about 20%, the total sample size would need to be 80 participants, which would ensure 80% power to demonstrate significance with a *p*-value < 0.05. To further enhance the statistical power, the sample size was ultimately set to 60 participants/cases per group, with a total of 120 patients to be included in the study.

#### 4.10.2. Statistics

The intergroup and intragroup differences in age, anthropometric parameters, and IBS symptom data across subsequent visits or weekly data from patient diaries or telephone interviews will be evaluated with two-sided paired or unpaired *t*-tests or repeated measures (RM) ANOVA after checking for equality of variances and normality of distribution using a Shapiro–Wilk test. If the data is not normally distributed, two-sample Wilcoxon paired or unpaired signed-rank tests will be used. Fisher’s exact test will be used for analyses of variables presented as percentages. The threshold of significance for all analyses will be set at α = 0.05.

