### 3.1. Inclusion Criteria

Patients with any of the following forms of IBS will be included:IBS-D—more than 25% of BSF type 6 and 7 stools, and less than 25% of type 1 and 2 stools;IBS-C—more than 25% of BSF type 1 and 2 stools, with less than 25% of type 6 and 7 stools;IBS-M—more than 25% of BSF type 6 and 7 stools and also more than 25% of type 1 and 2 stools.

To be eligible for the trial, subjects must meet all of the inclusion criteria and none of the exclusion criteria, as stated below.

The following inclusion criteria will be used:males and females aged from 18 to 70 years, inclusive;a good physical and mental condition assessed based on the patient’s history and physical examination;laboratory test results (complete blood count, blood chemistry panel) within normal limits or considered not to be clinically significant by the investigator;a voluntarily provided written informed consent;IBS with at least moderate symptom severity, defined as an IBS-Severity Scoring System (IBS-SSS) score of >175 points [32];the ability to strictly adhere to the investigators’ instructions regarding study procedures and protocol requirements.

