## 4. Detailed Procedures

The following measurements will be performed:A physical examination—at each visit;Anthropometric measurements, including weight, height, body mass index (BMI), waist-to-hip ratio (WHR), and arm or calf circumference—at visit 0 and at weeks 4 and 12 of the study intervention;Nutritional status assessment and body composition analysis, including skin fold measurements and bioelectrical impedance analysis (BIA) with the use of a Bodystat machine—at visit 0 and at weeks 4 and 12 of the study intervention;IBS symptom severity assessment, with the use of IBS-SSS [32]—at visit 0 and at weeks 4, 8, and 12 of the study intervention, and with patient-rated (on a Likert scale) symptom severity from patient diaries—weekly;Improvement or worsening of IBS symptoms, with the use of the IBS-SSS, IBS-Global Improvement Scale (IBS-GIS), and IBS—Adequate Relief (IBS-AR) [33]—at weeks 4, 8, and 12 of the study intervention;Adverse events based on the data from telephone interviewers and obtained by the investigators during the whole trial;Quality of life (QOF) assessment, with the use of IBS-QOL questionnaire [34]—at visit 0 and at weeks 4 and 12,Laboratory tests (including complete blood count; liver function tests (ALT, AST); bilirubin, amylase, creatinine, C-reactive protein, glucose, and electrolyte levels at the screening visit; and cytokine (interleukin 6 (IL-6) and macrophage inflammatory protein 1β (MIP-1ß)) levels at visit 0 and at weeks 4 and 12 of the study intervention.

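### The statistics section names no between-group efficacy contrast, leaves the collected baseline out as a covariate, and specifies a signed-rank test for unpaired data

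*Protocol article*

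**What the plan says.** Section 4.10.2 (Statistics) is the article's only statement of the analysis.

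- **Comparisons.** It covers "The intergroup and intragroup differences in age, anthropometric parameters, and IBS symptom data across subsequent visits" as well as weekly diary and telephone data. Between-group and within-group comparisons share one sentence, and neither is marked as the test of efficacy.
- **Tests.** These differences "will be evaluated with two-sided paired or unpaired" t-tests or repeated measures ANOVA, "after checking for equality of variances and normality of distribution". No covariate is named.
- **Fallback.** "If the data is not normally distributed, two-sample Wilcoxon paired or unpaired signed-rank tests will be used".
- **Percentages.** Fisher's "exact test will be used for analyses of variables presented as percentages".
- **Alpha.** "The threshold of significance for all analyses will be set at α = 0.05".

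Section 4 (Detailed Procedures) schedules IBS-SSS "at visit 0 and at weeks 4, 8, and 12 of the study intervention", and IBS-QOL at visit 0 and weeks 4 and 12, so both scales have a baseline. Section 4.8 defines the primary outcome as changes on IBS-SSS, IBS-GIS, IBS-AR and IBS-QOL, without saying that the change is to be compared between arms.

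**The concern.** Four features of this paragraph weaken the efficacy analysis.

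1. **No designated contrast.** Only the difference between randomised arms measures the effect of the product. Patients enter on IBS severity, "defined as an IBS-Severity Scoring System (IBS-SSS) score of >175 points", so some improvement in both arms is to be expected from regression to the mean and placebo response. A within-group p-value cannot separate that from a product effect. As written, nothing stops a significant change in the active arm from standing as the result.
2. **Baseline not used as a covariate.** The scores are available, and adjusting for them is the most precise standard use of them.
3. **A test that does not fit the data.** The signed-rank test works on within-pair differences. Two independent arms have no pairs.
4. **The quantity compared is left to the data.** After the normality check the analysis is either a difference in means or a shift in ranks, and this may differ between outcomes and visits.

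At stake are an avoidable loss of precision, a fallback rule that cannot be carried out as named, and a non-comparative result being read as efficacy.

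**Working it through.** **Inputs from the protocol.** Section 4.10.1 gives 35 per group, 80% power, p < 0.05, about 20% drop-out and a final 60 per group. No effect size, SD or baseline correlation is given.

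**The protocol's own figures.** The 35 cannot be reproduced without an effect size, but it can be solved backwards (two-sided 0.05): d = (1.960 + 0.842) × √(2/35) = 0.67. Separately, 35/0.8 = 43.75, so 44 per arm or 88 in total, not the stated 80. That does not affect this point, because 120 will be enrolled. With 20% loss, 60 × 0.8 = 48 completers per arm.

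**Precision.** Assume equal SD at baseline and week 12 (set to 1) and correlation r. The variances are:
- final score: 1
- change score: 2(1 − r)
- ANCOVA: 1 − r²

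Relative to the change score, ANCOVA variance is (1 − r²)/[2(1 − r)] = (1 + r)/2, that is 0.65, 0.75 and 0.85 at r = 0.3, 0.5 and 0.7.

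Two-sided t-test power with 48 per arm and d = 0.67 divided by the square root of each variance:

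| Assumed r | Final score | Change score | ANCOVA |
|---|---|---|---|
| 0.3 | 90.1% | 78.4% | 92.6% |
| 0.5 | 90.1% | 90.1% | 96.3% |
| 0.7 | 90.1% | 98.7% | 99.5% |

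ANCOVA gains 2.5, 6.2 and 9.4 points over the final score, and 14.2, 6.2 and 0.8 points over the change score. It is never the worse choice.

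**Within-group reading.** Suppose there is no product effect and both arms improve by the same standardised mean change w (mean change divided by its SD). The chance that one arm is significant is p = Φ(w√n − 1.96). The chance that active is significant and placebo is not is p(1 − p).

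| w (assumed) | p, n = 48 | p(1 − p), n = 48 | p(1 − p), n = 60 |
|---|---|---|---|
| 0.2 | 0.283 | 20.3% | 22.5% |
| 0.3 | 0.547 | 24.8% | 23.0% |
| 0.4 | 0.791 | 16.5% | 11.1% |
| 0.5 | 0.934 | 6.2% | 2.7% |

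A valid two-sided between-group test at 0.05 falsely favours active 2.5% of the time. The rate falls at larger w only because both arms then become significant, which is equally uninformative about the product.

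**Normality gate.** In a simulation under no effect (60 per arm, 4,000 runs per distribution; Shapiro-Wilk in each arm, then t-test or rank-sum test), type I error was 5.2% for normal data, 4.4% for log-normal and 5.0% for t with 5 df. With normal data the procedure still moved to ranks in 9.9% of runs. The gate does not materially inflate error; it leaves open which quantity is estimated.

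**The case against.** The strongest reply is that this is a condensed article about a placebo-controlled trial. It names the between-group comparison first, and nothing in it says that within-group results will be claimed as efficacy. An unadjusted randomised comparison is valid, so ANCOVA is a preference about precision, and a covariate model is detail that an analysis plan may hold. A change score or a group-by-time term in the repeated measures ANOVA does use baseline, if less efficiently. The unpaired signed-rank wording is probably a slip for the rank-sum test.

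Much of this stands, and it limits the size of the point. It does not remove it. The paragraph lists its tests and sets one alpha for all of them, so the missing designation and the wrong test name are in what it states. It does not say that the ANOVA will test group by time.

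A reader might infer stronger things that the documents do not support:

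- **That the entry cut-off makes a switch to rank tests likely.** With an assumed normal IBS-SSS (mean 250, SD 80) cut at 175 and 60 patients, Shapiro-Wilk rejects in roughly 62% to 65% of samples at baseline. For a jointly normal week-12 or change score it rejects only about 5% to 7%, close to the nominal rate.
- **That a signed-rank p-value would depend on row order.** This needs patients in different arms to be paired arbitrarily, which nobody proposes.
- **That the unadjusted test is underpowered.** This needs an effect such as 0.5 SD, which is not in the documents. At the implied 0.67 the unadjusted final score has about 90% power.
- **That Shapiro-Wilk is meant to check equal variances.** The sentence reads more naturally with that test attached to normality alone.
- **That the pre-test inflates type I error.** The simulation does not show it.

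**Conclusion.** The point holds in a moderate form and should be acted on. The test named for unpaired data is wrong. The between-group contrast is not designated as the efficacy test. Baseline scores already scheduled for collection are not named as covariates.

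Reading within-group p-values as efficacy would carry a false-claim rate of about 6% to 25% at 48 per arm, against 2.5%. This rests on an assumed standardised change of 0.2 to 0.5 that is equal in both arms. The power gain from adjustment rests on the implied effect of 0.67, 20% loss, and r between 0.3 and 0.7, none of which can be checked against source data here. Restricting entry to scores above 175 may pull r towards the lower end, where the gain over the final score is small and the gain over the change score is largest. The trial is not short of power on its own figures, and the comparisons it lists are not invalid for being unadjusted.

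**What to change.** Rewrite section 4.10.2, or state the following in the analysis plan before unblinding:

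- Make the efficacy test for IBS-SSS the between-group difference at week 12, from ANCOVA or a mixed model over weeks 4, 8 and 12, with the baseline score as covariate and a 95% CI. Do the same for IBS-QOL with its own visits.
- Compare IBS-GIS between arms by ordinal regression and IBS-AR by logistic regression. Neither has its own baseline; baseline IBS-SSS may serve as covariate.
- Remove the normality gate.
- Replace the unpaired signed-rank test with the rank-sum (Mann-Whitney) test, kept as a sensitivity analysis.
- Report within-group changes descriptively, without p-values.

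This costs one paragraph. It needs no new data, visits or patients.

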### 4.3. IBS-AR

IBS-AR is a dichotomous single-item questionnaire that asks participants “Over the past week, have you had adequate relief of your IBS symptoms?” The answer can be YES or NO.

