### 4.6. Patient’s Diary

Participants will be asked to fill out a diary every day. The diary will contain information on the number of bowel movements per day, the type of stools, and the severity of the following symptoms: abdominal pain, bloating, fecal urgency, and feeling of incomplete evacuation. The type of stools will be assessed using the BFS scale. Specific IBS symptoms, except for the feeling of incomplete evacuation, will be assessed using a patient-rated 5-point Likert scale, with 0 points indicating no symptoms, and 1–4 points indicating various levels of symptom severity, with higher scores indicating worse symptoms. The feeling of incomplete evacuation will be assessed using a 2-point scale, with 0 points indicating no such feeling and 1 point indicating the feeling of incomplete evacuation.

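### Fisher's exact test is assigned to every percentage variable, although the plan also makes within-group comparisons over time, so repeated yes/no outcomes would get an unpaired test

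*Protocol article*

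**What the plan says.** The first sentence of section 4.10.2 sets the scope: "The intergroup and intragroup differences in age, anthropometric parameters, and IBS symptom data across subsequent visits or weekly data from patient diaries", and also data from telephone interviews. For these it names "two-sided paired or unpaired *t*-tests or repeated measures (RM) ANOVA", with Wilcoxon tests, paired or unpaired, if the data are not normal. Percentages get one sentence: "Fisher’s exact test will be used for analyses of variables presented as percentages". No paired or repeated method is named for binary data. The section closes with "The threshold of significance for all analyses will be set at α = 0.05".

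Two efficacy variables are binary and repeated within patients:

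- **IBS-AR.** Section 4.3: "IBS-AR is a dichotomous single-item questionnaire" and "The answer can be YES or NO". Section 4 schedules it at weeks 4, 8 and 12, with no baseline value. Section 4.8 lists it among the four primary instruments, and the abstract sets the primary outcomes after 12 weeks.
- **Incomplete evacuation.** Section 4.6: "The feeling of incomplete evacuation will be assessed using a 2-point scale", scored 0 or 1 in a diary kept every day. Section 2.2 starts the diary in the 7-day run-in, so this item has pre-treatment data.

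Adverse events are also scored 0/1, from weekly telephone calls (section 4.7).

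**The concern.** The authors provide for within-patient dependence when the data are scores, but not when they are proportions. Fisher's exact test treats the two columns of a 2×2 table as independent samples. Within one group, the week-4 and week-12 answers come from the same patients and are likely to be positively correlated. An unpaired test then overstates the standard error of the change, so its false-positive rate falls far below 5% and real changes are missed.

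A second, separate matter is the between-arm comparison of IBS-AR, a primary measure. There each patient contributes one answer and nothing is violated. But Fisher's test is known to fall short of its nominal level, and the rule leaves no room for the baseline IBS-SSS that the trial collects anyway.

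An analysis plan that followed section 4.10.2 as written would inherit both features.

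**Working it through.** **Inputs.** From the protocol: 60 per group and about 20% drop-out (section 4.10.1), so 60 × (1 − 0.20) = 48 evaluable per group; two-sided α = 0.05 (section 4.10.2). Not given, so assumed: relief rates and within-patient correlation. The sample size section gives no response rates and no power for IBS-AR, so there is no figure of the plan's own to reproduce.

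**1. Within one group, two visits, 48 patients.** Paired answers are generated from a latent bivariate normal with correlation ρ. With rates p1 and p2:

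- p11 = Φ₂(z(p1), z(p2); ρ), p10 = p1 − p11, p01 = p2 − p11.

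The true variance of the change is [p10 + p01 − (p01 − p10)²]/n. The unpaired variance is [p1(1 − p1) + p2(1 − p2)]/n. For 35% to 55%:

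- Unpaired: 0.2275 + 0.2475 = 0.475.
- ρ = 0.5: p10 = 0.0825, p01 = 0.2825; true value 0.365 − 0.040 = 0.325. The standard error is overstated by √(0.475/0.325) = 1.21.
- ρ = 0.7: p10 = 0.0489, p01 = 0.2489; true value 0.2978 − 0.040 = 0.2578. Overstated by √(0.475/0.2578) = 1.36.

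Summing the multinomial probabilities of all tables that each test rejects at p < 0.05 gives:

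| Latent ρ | Fisher size (35% at both visits) | Fisher power (35% to 55%) | Exact McNemar size | Exact McNemar power |
|---|---|---|---|---|
| 0.5 | 0.8% | 41.1% | 2.7% | 57.5% |
| 0.7 | 0.3% | 39.8% | 2.4% | 67.9% |

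Fisher's test loses 57.5 − 41.1 = 16 points and 67.9 − 39.8 = 28 points.

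**2. Sensitivity to the correlation.** Simulation with 60 patients, 40% to 60%, 6,000 runs per scenario: Fisher's power stays at 54% to 55% throughout. McNemar's is 51% at ρ = 0, 59% at 0.3, 68% at 0.5, 81% at 0.7 and 86% at 0.8. With no correlation, Fisher's test loses nothing; the loss appears and grows as correlation rises.

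**3. Between arms, IBS-AR at week 12.** One answer per patient, so

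- rejection probability = Σₐ Σ_b Bin(a; n, p1) · Bin(b; n, p2) · 1[p(a, b) < 0.05].

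| Per arm | Fisher size (common rate 30% to 50%) | Fisher power, 35% v 60% | Chi-square power | Gap |
|---|---|---|---|---|
| 48 | 2.9% to 3.2% | 62.7% | 70.3% | 7.6 points |
| 60 | 3.1% to 3.5% | 74.7% | 80.3% | 5.6 points |

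For an assumed 40% v 60%, power is 42.8% v 51.1% at 48 per arm and 54.0% v 61.2% at 60. Uncorrected chi-square has size 5.0% to 5.2% at 48 per arm and up to 5.5% at 60, so part of its advantage is bought by using the full nominal level.

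**The case against.** The strongest reply is that the comparison that matters is between arms at week 12, and there Fisher's test is sound. This stands. A reader might infer that dependence between visits invalidates the primary IBS-AR test or costs it power. The documents do not support that: the abstract fixes the outcome after 12 weeks, each patient then gives one answer, and the shortfall in step 3 is Fisher's ordinary conservatism. Preferring a less conservative test is a matter of efficiency, not of correctness.

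A reader might also infer inflated false positives from treating days, stools or visits as independent units. The protocol plans no such pooling. Section 4 lists diary symptom severity as weekly, and section 4.10.2 puts weekly diary data in the sentence on t-tests, RM ANOVA and Wilcoxon tests. On that reading, incomplete evacuation would become one weekly value per patient and never reach Fisher's test. The text does not say how the daily 0/1 answers become a weekly figure, so both readings remain open.

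Three further points reduce the weight. IBS-AR has no baseline, so a within-group test can only compare on-treatment visits, which is not the efficacy contrast. The within-group error is in the conservative direction. And this is a condensed article whose analysis plan is not shown, so the absence of a named McNemar or GEE method would not by itself be a finding. What remains is that the article states a rule covering all percentages, in a section whose stated scope includes comparisons for which that rule is wrong.

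Finally, 48 per arm is an assumption. Section 3.3 records withdrawals as treatment failures; counting them as non-responders would keep 60 per arm but lower the relief rates.

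**Conclusion.** The point holds in limited form. Taken literally, section 4.10.2 applies an unpaired test to paired binary data in within-group comparisons. With 48 patients and latent correlation 0.5 to 0.7, the size is 0.3% to 0.8%, and power for 35% to 55% is about 40% instead of 57% to 68%. The week-12 between-arm test of IBS-AR is valid. It gives up about 6 to 8 points of power to chi-square for an assumed 35% v 60%, and makes no use of baseline severity. All rates and correlations are assumptions; at zero correlation the within-group loss disappears.

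This should be corrected before unblinding, because it touches a primary instrument and the wording would carry into the analysis. It does not threaten the validity of the primary comparison.

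**What to change.** Replace the sentence on percentages in section 4.10.2 with four rules:

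- **Fisher's exact test** only for between-arm comparisons with one observation per patient, such as patients with at least one adverse event, or as a sensitivity check on IBS-AR at week 12.
- **Within-group and multi-visit binary data:** McNemar's test for two time points, or a repeated-measures logistic model (GEE with robust standard errors) for more.
- **IBS-AR between arms:** the week-12 contrast from a logistic model, or from a GEE over weeks 4, 8 and 12 with arm, week and arm-by-week terms, adjusted in either case for baseline IBS-SSS.
- **Daily 0/1 items:** reduce to one value per patient per week before any comparison.

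The gain from the third rule should not be oversold. With complete data, an unadjusted GEE with full arm-by-week terms gives the week-12 logistic Wald test, whose power at 48 per arm (70%) equals that of chi-square. Anything beyond that must come from baseline adjustment or from patients with incomplete visits, and the documents give no figures to size it.

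The cost is a few lines of text and slightly more programming, with no new data collection. One small drawback is that an adjusted odds ratio is harder to read than a raw percentage, so the raw percentages should be shown beside it.

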## 5. Expected Results and Discussion

To the best of our current knowledge, this is the first randomized, double-blind, and placebo-controlled trial assessing the role of a mixture of colon-targeted microencapsulated sodium butyrate, probiotics, and small amounts of prebiotics in IBS patients. We believe that such a combination will help restore the disturbed functionality of the intestinal microbiota and increase intestinal levels of butyrate, which may benefit patients with IBS. The beneficial effects of probiotics and synbiotics in IBS patients were demonstrated in several randomized clinical trials [22,23,24,35], but only one study showed the superiority of butyric acid supplementation in comparison with placebo [20]. The efficacy of biotics in IBS depends on preparation composition, dose, and duration of administration [36]. In the present study, we plan to use a combination of sodium butyrate with a probiotic mixture and prebiotic scFOS. We have decided on this composition taking into account our previous research on the effects of a synbiotic product with the same composition of probiotic strains and prebiotic scFOS. In that previous randomized placebo-controlled clinical trial we demonstrated that this specific probiotic mixture containing three *Bifidobacterium* species (*Bifidobacterium lactis*, *Bifidobacterium longum*, *Bifidobacterium bifidum*), two *Lactobacillus* species (*Lactobacillus rhamnosus*, *Lactobacillus acidophilus*), and scFOS significantly decreased the total IBS-SSS score in IBS-D patients [27]. This beneficial effect was mainly achieved by improvement in bloating; however, no effect on the perception of pain was observed. Given that butyric acid has been shown to decrease the severity of both abdominal pain and the feeling of incomplete evacuation [20], we hypothesize that the addition of colon-targeted microencapsulated sodium butyrate plus small amounts of scFOS to this specific probiotic mixture would further enhance the effectiveness of the intervention against a wider range of clinical symptoms.

Changes in gut microbiota composition differ depending on the type of IBS [14]. In a study by Pozuelo et al., a lower abundance of butyric acid-producing bacteria was mainly observed in patients with IBS-D and IBS-M [15]. In contrast, El-Salhy et al. [37] found propionate and butyrate levels to be reduced in IBS-C patients, and butyrate levels to be increased in IBS-D patients in comparison with the control group. We plan to enroll patients with all three types of IBS (IBS-D, IBS-C, and IBS-M). Thus, the current study will allow us to determine in which type of IBS patients the study combination of butyrate sodium, probiotics, and small amounts of scFOS has the best effectiveness.

In our study, we have decided to administer the butyrate sodium + probiotics + scFOS preparation for 12 weeks, which allows us to expect an improvement in specific IBS symptoms measured with the use of international scales (IBS-SSS, IBS-GIS, IBS-AR) and patients’ QOL. As SCFAs (including butyric acid) have been estimated to provide about 10% of the total dietary energy supply in humans [38] and may also stimulate lipogenesis [39] we have planned to assess the impact of SCFA supplementation on body composition, anthropometric measurements, and BMI. We also suspect that a combination of sodium butyrate, probiotics, and small amounts of prebiotics will affect the inflammatory processes present in IBS patients, which we will be able to demonstrate by analyzing selected serological biomarkers (IL-6, MIP-1ß).

Our study has many strengths, most notably the design of a randomized, double-blind placebo-controlled trial, weekly monitoring of participants by interviewers, and assessment of primary endpoints on international scales. However, there are also some limitations. Due to budget constraints, we do not plan to assess the changes in microbiome composition, which may allow us to better explain the mechanism of clinical effects as well as the post-interventional visit to assess the longevity of the response to the intervention. Additionally, the amount of prebiotic scFOS that will be used in this trial is much lower than the amounts used in previous trials, and these small amounts may not be sufficient to have a meaningful physiological effect. This limitation was dictated by the practical size of the capsules. The inclusion of more scFOS would result in too large a capsule size. Nonetheless, we expect the inclusion of colon-delivered microencapsulated sodium butyrate to compensate for the small amounts of scFOS and possibly even show additional beneficial effects. It is important to emphasize that butyric acid is the topic of ongoing discussions as an SCFA and a beneficial metabolite of gut microbiota potentially useful as a postbiotic, although there is currently no consensus [40,41].

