### 2.3. Randomization

The subjects will be randomly assigned to study groups (receiving butyrate sodium + probiotics + scFOS or placebo) according to a computer-generated randomization list. In order to ensure a balance in the sample size across groups over time, a block randomization model will be applied, with a block size of 4 [28]. The block size will not be disclosed to the investigators, and both the investigators and the patients will be blinded to group allocation.

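### The article says the trial will determine which IBS type benefits most, but 120 patients sized for one overall comparison cannot rank three types

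*Protocol article*

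**What the plan says.** Section 5 (Expected Results and Discussion) reviews conflicting findings on butyrate and butyrate-producing bacteria across IBS types, then says "We plan to enroll patients with all three types of IBS (IBS-D, IBS-C, and IBS-M"). From this it concludes that "the current study will allow us to determine in which type of IBS patients the study combination of butyrate sodium, probiotics" and scFOS is most effective. Enrolling all three types is the only support offered. The limitations listed later in the same section do not mention precision by subtype.

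Section 4.10.1 (Sample Size Calculation) concerns a single comparison of two groups. It states that "a sample size of 35 participants per group would be required to reach clinical significance" and continues: "With an estimated drop-out ratio of about 20%, the total sample size would need to be 80 participants". It credits that size with 80% power at p < 0.05. The target was then raised: "the sample size was ultimately set to 60 participants/cases per group, with a total of 120 patients". The reason given is more statistical power in general, not subtype analysis. The calculation draws on the sponsor's previous synbiotic trial, whose IBS-SSS result section 5 describes as obtained in IBS-D patients.

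Section 3.1 sets no minimum or expected share per subtype. Section 4.10.2 adds: "The threshold of significance for all analyses will be set at α = 0.05".

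**The concern.** Enrolling three types of patient is not the same as being able to rank treatment effects among them. Ranking needs a comparison of effects between subtypes, which is much less precise than the overall comparison for which the trial was sized.

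At stake is how the subtype results will be read. With small subgroups and a 0.05 threshold for every analysis, a mixed pattern (significant in one type, not in another) is the expected outcome even when the types do not differ. A published statement that the trial can determine the best type invites readers to take such a pattern as an answer.

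**Working it through.** **Inputs from the article.** 60 randomised per group; dropout about 20%; 35 per group for 80% power; α = 0.05; two-sided tests (section 4.10.2); three subtypes.

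**Assumptions, because the article gives no figure.**
- Effect size: back-solved from 35 per group. The endpoint, mean difference and SD are not stated.
- Subtype shares: equal thirds, with 50/30/20 as an alternative.
- Dropout: 20%, with none as an alternative.

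**1. The article's own figure.** The 35 per group cannot be rebuilt without an effect size, so I inverted it.
- Normal approximation: d = (1.960 + 0.842) × √(2/35) = 0.67.
- t-test: d = 0.68.

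The dropout step does not give 80 either: 35/0.80 = 43.75, rounded up to 44 per group or 88 in total, and 35 × 1.20 = 42 per group or 84 in total. This does not affect the present point, because 120 are to be enrolled.

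**2. Overall comparison.** Evaluable per arm: 60 × 0.80 = 48. Power at d = 0.68 is about 91%, so the overall comparison is well served.

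**3. Within one subtype.** 48/3 = 16 evaluable per arm. Two-sample t-test power at d = 0.68:

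| Scenario | Evaluable per arm, by subtype | Power |
|---|---|---|
| Equal thirds, 20% dropout | 16 each | 46% |
| Equal thirds, no dropout | 20 each | 55% |
| 50/30/20 split, 20% dropout | 24 / 14.4 / 9.6 | 63% / 42% / 29% |

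**4. Between two subtypes.** This is the comparison that ranking needs. In SD units, the standard error of the difference between two subtype effects is √(2/n₁ + 2/n₂). Approximate power for a true difference of 0.68, the whole planning effect, is Φ(0.68/SE − 1.96).
- 16 against 16: SE = √(4/16) = 0.50; power 27%.
- 20 against 20 (no dropout): SE = √(4/20) = 0.447; power 33%.
- 50/30/20 split: SE = 0.471 (24 against 14.4), 0.540 (24 against 9.6) and 0.589 (14.4 against 9.6); power 30%, 24% and 21%.

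The difference detectable with 80% power at 16 per arm is 2.80 × 0.50 = 1.40 SD, about twice the planning effect. This figure does not depend on the back-solved d. With no dropout it is 2.80 × 0.447 = 1.25 SD.

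**5. Size needed.** For 80% power on one such pairwise contrast, n = 4 × (1.960 + 0.842)²/d². With d² = (1.960 + 0.842)² × 2/35, this is exactly 2 × 35 = 70 evaluable per arm per subtype. That makes 6 × 70 = 420 evaluable, and 420/0.80 = 525 randomised.

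**6. Chance of a misleading pattern.** Suppose the true effect is 0.68 in every subtype. The probability that some subtype tests are significant and others are not is 1 − p³ − (1 − p)³. With p = 0.46 this is 1 − 0.097 − 0.157 = 0.745, about 75%. With no dropout (p = 0.553) it is 1 − 0.169 − 0.089 = 0.74.

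**7. Ranking by point estimate.** If one subtype truly had d = 0.67 and the other two half of that, simulation at 16 per arm puts the truly best subtype first only 62% of the time.

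**The case against.** The strongest reply is that this is one sentence in a discussion section. The aim and hypothesis (section 2.1) concern IBS patients as a whole, and the endpoints (section 4.8) contain no subtype comparison. That is correct, and it limits the point. Ranking subtypes is not a stated aim, no primary test depends on it, and the article does not say that a chance pattern will be reported as a finding. The sentence is still a prospective, unqualified claim about what the trial can show.

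Three stronger readings are tempting, and the article does not support them.

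- *That the listed methods force separate p-values within each subtype.* Section 4.10.2 includes repeated-measures ANOVA, which can carry a subtype factor and an interaction. The subgroup method may also sit in an analysis plan that is not shown, so its absence here is no fault.
- *That randomisation is unstratified.* Section 2.3 says that "a block randomization model will be applied, with a block size of 4" and names no stratification factor. It does not say there is none.
- *That lack of stratification would undermine the subtype comparison.* Unstratified allocation still gives valid comparisons within subtypes. A 24:16 split in place of 20:20 raises the standard error from √(2/20) = 0.316 to √(1/24 + 1/16) = 0.323, about 2%.

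It is also fair to object that 16 per arm and d = 0.68 are not the article's figures. Under each alternative tried, however, between-subtype power stays at or below 33%.

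**Conclusion.** The point holds as an overclaim. The article attributes to the trial an ability to identify the best-responding IBS type that its size cannot provide. The within-subtype, between-subtype and mixed-result probabilities rest on an effect size inverted from 35 per group and on assumed subtype shares. The 1.4 SD detectable difference needs only the share and dropout assumptions. Since the planning trial's result is described for IBS-D, the article also offers no planning effect for IBS-C or IBS-M. No analysis plan, seen or unseen, could make up the gap between 120 patients and the roughly 525 that one pairwise contrast would need under these assumptions. The defect lies in the claim, not in the validity of the overall comparison. It should be corrected, because the correction costs almost nothing.

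**What to change.** Replace the sentence in section 5 with one saying that subtype effects are exploratory and that the trial is not powered to rank them. Base any subtype statement on a single treatment-by-subtype interaction test, reported with the treatment estimate and confidence interval for each subtype, and not on separate within-subtype p-values.

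The cost is a softer claim and one additional exploratory analysis; sample size and endpoints do not change. Stratifying the randomisation list by subtype is optional. It would bring a small gain in precision but would not cure the low power.
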